**Project summary**

**Background:** Low back pain (LBP) is a very common problem among different age groups. Previous studies into LBP assessed the effects of physical interventions or face-to-face (FTF) education mostly in western cultures.

**Study aim**

The present study aim to compare to compare the effects of multimedia and FTF pain management education (PME) on pain intensity and pain catastrophizing among patients with chronic LBP.

**Design**Double-blind randomized controlled clinical trial on ninety patients with chronic LBP. Participants will be randomly allocated to either multimedia, FTF, or control groups through block randomization.

**Settings and conduct**

Participants in the multimedia group will receive PME through watching seven educational CDs at home and their counterparts in the FTF group receive the same educations in seven weekly FTF educational sessions. Pain intensity and pain catastrophizing will be assessed before, immediately after, and one month after the study intervention.

**Rationale & background information**

Low back pain (LBP) is a common type of chronic pain ([Zernikow, Kriszio, Frosch, Dobe, & Wager, 2019](#_ENREF_32)) which affects 57.6 million people in the world ([Vos et al., 2017](#_ENREF_30)). LBP imposes a heavy burden on healthcare systems so that almost three fourth of all pain-related healthcare costs are spent on LBP management ([Fourney et al., 2011](#_ENREF_9)). It not only causes physical and financial problems, but also negatively affects the mental status and the social activities of afflicted patients and their families ([Ojeda et al., 2014](#_ENREF_19)).

We know that chronic pain has different biopsychosocial aspects and hence, its management should be based not only on physical factors, but also on psycho-social factors ([Ramond et al., 2011](#_ENREF_20)). The Fear Avoidance Model illustrates that some psychological factors such as pain catastrophizing can lead to avoidance, depression, and disability among patients with chronic pain ([Linton & Shaw, 2011](#_ENREF_16)).

Pain catastrophizing is a cognitive process of exaggerating or magnifying pain perception which results in greater attention to the negative aspects of pain, interpretation of physical arousals as pain symptoms, and pain intensity ([Turner & Aaron, 2001](#_ENREF_29)). Besides pain catastrophizing, factors such as stress, anger, poor communication skills, and limited assertiveness can affect pain intensity among patients with chronic conditions. For example, a study found stress, social conflicts, and non-assertive relationships as aggravating factors of chronic pain ([Ashton-James & Ziadni, 2020](#_ENREF_2)). Studies into occupational therapy for chronic pain also emphasize that patients with limited problem solving, communication, and assertiveness skills may have problems in pain management ([Hill, 2016](#_ENREF_12)). Consequently, besides physical interventions, education of psychological skills such as stress management, assertiveness, effective communication, positive thinking, and anger management should be included in pain management programs ([Andersson, Johansson, Nordlander, & Asmundson, 2012](#_ENREF_1)).

Previous studies reported contradictory results respecting the effects of outpatient psychological interventions such as cognitive behavioral therapy on chronic pain management in adults ([Tse, Yeung, Lee, & Ng, 2016](#_ENREF_28)). For example, a systematic review on nineteen studies found that there was no clear evidence concerning the effects of cognitive behavioral therapy, biofeedback, and relaxation on pain intensity and disability among patients with neck pain ([Shearer et al., 2016](#_ENREF_23)). A recent meta-analysis on eleven clinical trials also found no significant difference between the long-term effects of psychological interventions and standard interventions on pain intensity ([Bérubé et al., 2021](#_ENREF_3)). Besides contradictory results, previous studies mostly focused on one aspect of pain (either physical or psychological), while chronic pain is a complex experience and hence multidisciplinary interventions are needed for its effective management ([Zernikow et al., 2019](#_ENREF_32)). On the other hand, patients who live far from pain management centers may have limited access to multidisciplinary pain management services. Therefore, tele-nursing methods such as multimedia education are needed to improve patient access to pain management services and remove the barriers to evidence-based treatments.

Some previous studies evaluated the effects of technology-based pain management programs ([Garg, Garg, Turin, & Chowdhury, 2016](#_ENREF_10); [Vugts, Joosen, van der Geer, Zedlitz, & Vrijhoef, 2018](#_ENREF_31)). However, most of them were web-based programs ([Garg et al., 2016](#_ENREF_10); [Nevedal, Wang, Oberleitner, Schwartz, & Williams, 2013](#_ENREF_18)), single-center, and non-controlled ([Bérubé et al., 2021](#_ENREF_3); [Shearer et al., 2016](#_ENREF_23)). Moreover, there are limited comparative studies into the effects of FTF and multimedia pain management programs ([Suman, Schaafsma, Bamarni, Van Tulder, & Anema, 2017](#_ENREF_26); [Suman et al., 2018](#_ENREF_27)). On the other hand, the results of the existing studies in this area may not be generalizable to different context because the effects of psychological factors on chronic pain largely depend on patients’ sociocultural background ([Kovacs et al., 2012](#_ENREF_15)). Nonetheless, most previous studies into pain catastrophizing and pain were conducted in northern European countries and Anglo-Saxon cultures ([Hirsh, George, Riley III, & Robinson, 2007](#_ENREF_13); [Moix, Kovacs, Martín, Plana, & Royuela, 2011](#_ENREF_17)). There is limited information in this area in the culture of Asian countries, particularly in Iran. Therefore, studies in different contexts and cultures are needed to provide more reliable results regarding the effects of multimedia pain management program on chronic LBP and pain catastrophizing ([Kovacs et al., 2012](#_ENREF_15)). All these gaps highlight the necessity of conducting further studies into pain catastrophizing among patients with chronic LBP and the comparative effects of face-to-face and multimedia treatments in this area. The present study was designed and conducted to reduce these gaps. The aim of the current study was to compare the effects of multimedia and face to face (FTF) pain management education (PME) on pain intensity and pain catastrophizing among patients with chronic LBP. The hypothesis of the present study was that patients with chronic back pain who receive FTF and multimedia PME will show significant decrease in pain intensity and pain catastrophizing, assessed immediately after program and at 1-month follow-up.

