**Study goals and objectives**

**Goal:**

Comparing the effects of multimedia and FTF pain management education (PME) on pain intensity and pain catastrophizing (PC) among patients with chronic LBP.

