**Objectives:**

- Determining the demographic variables of participants
- Determining and comparing the mean score of pain intensity within the interventions and control groups, before, immediately and one month after intervention
- Comparing the changes of the mean score of pain intensity between the intervention and control groups
- Determining and comparing the mean score of pain catastrophizing within the interventions and control groups, before, immediately and one month and after intervention
- Comparing the changes of the mean score of pain catastrophizing between the interventions and control groups

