***Wait-list control group***

Participants in the control group will receive routine care services. Participants in this group will be asked not to participate in any other educational programs during the study and will be provided with the multimedia educational CDs at the end of the study. All participants in all groups will complete the study instruments before, immediately after, and one month after the study intervention.

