**Data analysis**:

Data will be entered into the SPSS software (v. 22.0) and analyzed at a significance level of less than 0.05. The Kolmogorov-Smirnov test will be performed to test the normality of the study data. Data will be described via the measures of descriptive statistics, namely mean, standard deviation, absolute frequency, and relative frequency. Groups will be compared with each other using the Chi-square test (for categorical variables) or the one-way analysis of variance (for numerical variables). To analyze treatment effects, a repeated-measures multivariate analysis of variance (MANOVA) with Tukey’s post hoc test will be performed. Effect sizes will be reported where appropriate and calculated by Partial ɳ^2^. The following are small, medium, and large effects for ɳ^2^, respectively: .01, .06, and .14 ([Stevens, 1996](#_ENREF_24)). Clinical outcome (MDC) for pain intensity and catastrophizing will be also reported. MDC means that the participants with a change score smaller or equal to the MDC have a chance of more than 95% that no real change has occurred.

The regression model used in the present study will be Generalized Estimating Equations (GEE). GEE procedure extends the generalized linear model to allow for analysis of repeated measurements or other correlated observations. To do so, after choosing the “Generalized estimating equations”, in the “*Repeated”* tab, the time will be entered to the within-subject variables box, in the “*Type of mode”*, the linear icon will be chosen in the scale response box, and in the “*Response”* tab, the pain intensity/pain catastrophizing will be entered in the dependent menu. In the “*Predictors”* menu, we will enter the predictors “group, pain catastrophy and time” for pain intensity and “group, pain intensity and time” as the predictors for pain catastrophy.

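### The only stated hypothesis names no comparator: improvement shared by all arms could satisfy it, and it does not match the multimedia-versus-FTF goal or the planned between-group comparison

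*Protocol*

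**What the plan says.** The hypothesis closes the Rationale & background information section: "patients with chronic back pain who receive FTF and multimedia PME will show significant decrease in pain intensity and pain catastrophizing". It refers to two occasions, the end of the programme and one month later. No other hypothesis appears in the Protocol.

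The goal is a different question: "Comparing the effects of multimedia and FTF pain management education (PME) on pain intensity and pain catastrophizing (PC) among patients with chronic LBP". The sentence just before the hypothesis gives the same comparative aim.

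The Objectives contain two kinds of statement for each outcome and do not rank them. For pain, one is before-after: "Determining and comparing the mean score of pain intensity within the interventions and control groups, before, immediately and one month after intervention". The other is between groups: "Comparing the changes of the mean score of pain intensity between the intervention and control groups". No objective spells out multimedia against FTF.

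The comparator arm exists: "Participants in the control group will receive routine care services", and all groups complete the instruments at all three occasions (Wait-list control group).

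The Data analysis section sets the level ("analyzed at a significance level of less than 0.05", sidedness not given). For treatment effects it plans a repeated-measures MANOVA with Tukey post hoc tests. It adds a GEE whose listed predictors for pain are group, catastrophizing and time.

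**The concern.** A hypothesis fixes what a trial may claim. This one is met if scores fall significantly over time in patients who receive the two programmes. Natural course or routine care could produce that fall in every arm, including wait-list, so meeting the hypothesis would not show that education did anything. Nor would it say whether multimedia does better, worse or about as well as FTF, which is the stated goal.

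The rest of the Protocol only partly repairs this. The before-after objective fits the hypothesis as worded, and the between-group objective does not. Data analysis does not say whether the time, group or group-by-time effect decides the hypothesis. The GEE, as listed, has no group-by-time term. With group and time as main effects only, it imposes the same time course on every arm, so its group coefficient does not measure a difference in change.

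**Working it through.** **1. Match between sections**

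| Section | Question posed | Comparator |
|---|---|---|
| Rationale (hypothesis) | Do scores fall in educated patients? | None |
| Goal | Multimedia or FTF? | Other education arm |
| Objectives (within) | Do scores change over time in each group? | Baseline |
| Objectives (between) | Do changes differ, intervention against control? | Control |
| Data analysis | MANOVA with Tukey; GEE | Groups, but no deciding effect named |

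The hypothesis agrees only with the within-group row.

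**2. Size of the problem**

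The Protocol gives no power, effect size, SD or expected course, so there is no figure to reproduce and this is an illustration.

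Inputs from the Protocol:
- n = 30 per arm (90 patients in the Design summary, 90/3 = 30) or n = 36 per arm (Study design). The two sections differ, so both are shown.
- Significance level 0.05, taken as two-sided.

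Assumed inputs:
- No treatment effect.
- A common fall *d* of 0.5 or 1.0 NRS points in every arm.
- SD of change *s* of 1.5, 2.0 or 2.5.

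For one arm, the chance *p* of a significant fall is the upper-tail power of a paired t-test with n − 1 degrees of freedom and noncentrality (d/s)√n. For d = 1.0, s = 2.0, n = 30, the noncentrality is 0.5 × √30 = 2.74 and p = 0.754.

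The hypothesis names both education arms. They contain different patients, so the joint chance is p². In the same example, 0.754² = 0.568.

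| n | d | s | One arm, p | Both arms, p² |
|---|---|---|---|---|
| 30 | 1.0 | 1.5 | 0.942 | 88.7% |
| 30 | 1.0 | 2.0 | 0.754 | 56.8% |
| 30 | 1.0 | 2.5 | 0.563 | 31.7% |
| 36 | 1.0 | 1.5 | 0.973 | 94.7% |
| 36 | 1.0 | 2.0 | 0.831 | 69.0% |
| 36 | 1.0 | 2.5 | 0.646 | 41.7% |
| 30 | 0.5 | 1.5 | 0.423 | 17.9% |
| 30 | 0.5 | 2.0 | 0.262 | 6.9% |
| 30 | 0.5 | 2.5 | 0.184 | 3.4% |

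These figures are for one outcome at one time point. Also requiring a fall in catastrophizing, and at both time points, would lower them.

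**3. The between-arm alternative**

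In 20,000 simulated trials per setting (SD of change 2.0; common fall 0.5, 1.0 or 1.5; n = 30 or 36; no treatment effect), a one-way F-test of change across the three arms was significant in 4.8% to 5.2%. A fall shared by all arms cancels out of that test.

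**The case against.** The strongest reply is that this is one loosely worded sentence in a background section, and that the trial is plainly built to compare groups. It has a randomised wait-list arm, between-group objectives and a MANOVA with Tukey tests, which can compare all pairs of groups, including multimedia with FTF. Much of that stands. A reader might infer that the trial has no between-group analysis, or that it would judge efficacy by paired tests within arms. The documents do not support either: no paired within-arm test is planned, and Data analysis ties treatment effects to the MANOVA.

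Three other tempting readings also fail:
- **Regression to the mean.** It might be taken as certain. The Inclusion criteria set no minimum pain score, so selection on a high score is not established. Shared improvement is possible, but its size is unknown.
- **Single-arm percentages.** They might be read as the chance of confirming the hypothesis. The hypothesis is joint, so they overstate it. With a 0.5-point fall and n = 30, the joint chance is near or below 5% for two of the three SDs.
- **Adoption.** Expected outcomes of the study might be read as recommending the programmes after a mere before-after fall. It makes use conditional on efficacy being confirmed and does not define efficacy that way.

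What the reply leaves unanswered is the mismatch. The planned analyses are not tied to the hypothesis, and no objective names the contrast in the goal. A SAP may give model detail, but the hypothesis and objectives are fixed in the Protocol.

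**Conclusion.** The point holds as an inconsistency in what the trial sets out to show, and it should be fixed. The hypothesis can be met by improvement common to all arms, does not address the goal, and is not linked to a deciding effect in the analysis.

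How much this could matter depends on quantities that the Protocol does not give. With no treatment effect and a common fall of 1.0 point, both education arms would show a significant NRS fall at one time point in 32% to 89% of trials with 30 per arm, and in 42% to 95% with 36. With a fall of 0.5 points and 30 per arm the range is 3% to 18%. These figures assume a two-sided 5% paired test, which the Protocol does not plan, and they measure only how weak the hypothesis is as a criterion. They are not the trial's false-positive rate. The conclusion itself does not depend on the drift chosen: shared improvement can satisfy a criterion without a comparator and does not inflate a between-arm one.

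**What to change.** - **Rationale & background information:** restate the hypothesis as a greater fall in NRS pain than wait-list for multimedia and for FTF, each separately, with parallel wording for catastrophizing.
- **Objectives:** add an explicit multimedia-minus-FTF contrast, since that is the goal, and say whether it seeks superiority, equivalence or non-inferiority.
- **Data analysis:** state that efficacy is judged on these between-arm differences, adjusted for baseline and reported in NRS points with 95% confidence intervals. Say that within-arm changes are descriptive only.

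The cost is rewording three sections and a small change to the planned analysis. The scores are already due to be collected in every arm at all three occasions, so no extra data, visits or patients are needed.

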**Study goals and objectives**

**Goal:**

Comparing the effects of multimedia and FTF pain management education (PME) on pain intensity and pain catastrophizing (PC) among patients with chronic LBP.

**Objectives:**

- Determining the demographic variables of participants
- Determining and comparing the mean score of pain intensity within the interventions and control groups, before, immediately and one month after intervention
- Comparing the changes of the mean score of pain intensity between the intervention and control groups
- Determining and comparing the mean score of pain catastrophizing within the interventions and control groups, before, immediately and one month and after intervention
- Comparing the changes of the mean score of pain catastrophizing between the interventions and control groups

**Study design**

The participants will be randomly assigned to three groups each containing 36 participants receiving pain management education via multimedia or face to face (FTF) method and in control group no education will be performed.

**Participants**

The participants of the current study will be males and females aged over 18 years with non-specific chronic LBP recruited from three healthcare centers. All interested patients will be invited to participate in the research. Afterwards, the interested individuals will be selected based on other inclusion and exclusion criteria.

**Inclusion criteria:**

- age over eighteen years
- agreement for participation
- ability to use educational CDs
- ability to attend the study setting for participation in FTF PME sessions
- no affliction by other types of chronic pain (such as chronic headache
- no affliction by chronic psychological disorders (such as schizophrenia)
- definite diagnosis of non-specific chronic LBP established at least one month before the study by a medical specialist based on the data obtained through physical examination and diagnostic procedures such as simple radiography, computed tomography, or magnetic resonance imaging

**Exclusion criteria:**

- voluntary withdrawal from the study for any reason (such as severe LBP)
- participation in any other educational program on pain during the study
- more than two absences from the educational sessions of the study intervention.

**Expected recruitment start date**

2018-05-10
**Expected recruitment end date**

2019-05-10

**Methodology**

**Randomization description**

Participants will be randomly allocated to either the multimedia, FTF, or the wait-list control group. A research assistant not involved in the current study will perform random allocation through block randomization with a block size of 6 and cards labeled A, B, and C. Allocation concealment will be ensured using sequentially numbered, opaque, sealed envelopes (SNOSE) ([Clark et al., 2013](#_ENREF_5)).
**Blinding**The patients will be blinded to the patient group assignments and will not know what the other interventions will be. In addition, the evaluator and the analyzer of the outcomes will not be informed about the patients’ treatment assignments.

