**Interventions**

***Multimedia pain management education***

Eligible participants in this group will receive multimedia PME in seven weeks. The modules of this education will consist of definition of chronic pain and the psychological factors affecting pain experience (the first session), appropriate physical exercises for chronic LBP (the second session), effective communication skills (the third session), assertiveness skills (the fourth session), stress management skills (the fifth session), positive thinking skills (the sixth session), and anger management skills (the seventh session). Educational materials will be developed based on the existing literature on chronic pain management ([Dobson, 2010](#_ENREF_7); [Dobson & Dozois, 2010](#_ENREF_8)). Educational modules will consist of textual and audiovisual data. Each week during the study intervention, one of the CDs will be provided to participants and they will be asked to watch it at home in forty minutes. After watching two educational CDs, an FTF session will be held for answering the questions of participants in the multimedia group. Moreover, a WhatsApp group will be formed where the third author answered patients’ questions and encouraged them for using educational materials.

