***Face-to-face pain management education***

For participants in the FTF group, the third author will provide the same educational materials as multimedia group through the lecture, question-and-answering, and PowerPoint presentation methods in seven weekly sessions, each last 60–90 minutes. Participants in this group will receive educations in the form of small 8–10-person groups.

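### A single fixed block of 6, with no provision to keep the size or past allocations from those who enrol, leaves up to a fifth of allocations deducible

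*Protocol*

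**What the plan says.** Under Randomization description, patients are "randomly allocated to either the multimedia, FTF, or the wait-list control group", by "block randomization with a block size of 6 and cards labeled A, B, and C". One size is given, and nothing says that it varies or is withheld. Two safeguards are stated in the same place: "A research assistant not involved in the current study will perform random allocation", and the cards are kept in numbered, sealed opaque envelopes.

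The blinding statement that follows covers patients, the outcome evaluator and the analyst. It does not mention whoever enrols patients or delivers the education.

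The arms differ openly: CDs at home, weekly classes, or routine care with CDs only at the end. One member of the team serves both education arms. For the classes, "the third author will provide the same educational materials as multimedia group"; for the CD arm, "a WhatsApp group will be formed where the third author answered" patients' questions.

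The total is given in two ways. The Design paragraph under Study aim describes a "randomized controlled clinical trial on ninety patients with chronic LBP", while Study design describes "three groups each containing 36 participants", which makes 108. Participants come from three healthcare centres (Participants section). The protocol does not say who enrols them, whether that person sees earlier allocations, whether allocation is sequential or in batches, or whether blocks run within centre.

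**The concern.** Sealed envelopes and an outside allocator hide the next card. They do not stop someone from deducing it by counting the cards already used, if the block size is known and past assignments can be seen. With three equal arms, each block of 6 holds two cards per arm, so the end of a block gives itself away.

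This matters because some entry criteria need judgement, such as whether a patient can use the CDs or attend the sessions. A recruiter who expects a particular arm could apply them differently or delay a patient. The primary outcome is a self-rated 0–10 pain score, so patients selected for their expected response could bias the comparison of arms.

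**Working it through.** The protocol gives no figure for predictability, so there is none to reproduce.

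**Inputs**
- Block size 6, three arms (Randomization description).
- Two cards per arm in each block. This is inferred from the equal group sizes in Study design.
- Total of 90 (Design paragraph) or 3 × 36 = 108 (Study design), which is 15 or 18 complete blocks.

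**Worst case: the observer knows the size and all earlier allocations in the block**

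The number of distinct blocks is 6!/(2!·2!·2!) = 90, all equally likely. An allocation is certain when every card left in the block belongs to one arm.
- Positions 1 to 4: never certain, because at least three cards remain and no arm has more than two.
- Position 5: certain when the last two cards match, 18/90 = 0.20.
- Position 6: always certain, 1.

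Expected certain allocations per block = 1 + 0.20 = 1.2, and 1.2/6 = 20.0%. That is 0.20 × 90 = 18 patients, or 0.20 × 108 = 21.6. The share does not depend on which total applies.

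The best guess is always the arm with most cards left. Its expected hit rates at positions 1 to 6 are 1/3, 2/5, 1/2, 8/15, 3/5 and 1. They sum to 101/30 = 3.367, and 3.367/6 = 56.1%, against 33.3% by chance.

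**Favourable case: one sequence shared by the three centres, recruiter sees only local patients**

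Assume that each patient is equally likely to come from each centre, so each earlier allocation in the block is seen with probability 1/3. The recruiter is taken to know the position in the block.
- Position 5 is certain only if all four earlier cards were seen and form two pairs: (1/3)⁴ × 0.20 = 0.00247.
- Position 6 is certain if all five were seen, (1/3)⁵ = 0.00412, or if exactly four were seen and form two pairs, 5 × (1/3)⁴ × (2/3) × 0.20 = 0.00823. Together this is 0.01235.

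The sum is 0.01482 per block, and 0.01482/6 = 0.25%, or about 0.2 of 90 and 0.3 of 108 patients. Enumerating the 90 blocks with every pattern of seen and unseen cards gives a best-guess rate of 39.4%.

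**Effect of varying the block size**

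This was simulated over 1,000 trials of 108 patients. The observer knows all past allocations and the set of possible sizes, but not the size of the current block. The row for fixed 6 is the exact result above.

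| Block sizes | Certain in advance | Best guess right |
|---|---|---|
| 6 fixed | 20.0% | 56.1% |
| 3 and 6 | 8.6% | 57.7% |
| 3, 6 and 9 | 3.8% | 55.3% |
| 6 and 9 | 5.0% | 54.0% |

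Varying the size removes most of the certainty but hardly changes the best guess.

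**The case against.** The case against is substantial. The main safeguards are in place, and fixed permuted blocks are a recognised method. The 20% needs an observer whom the protocol never supplies. The team member who teaches one arm and supports the other is not said to enrol patients or open envelopes. Membership of a class or chat group shows neither the order of the envelopes nor, by itself, who went to control. Classes of 8–10 people need roughly 24 to 30 patients allocated 1:1:1 to fill one group; if these were enrolled first and allocated together, prediction could not influence selection.

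Timing is a further point. Recruitment was expected from May 2018 to May 2019, yet this text cites 2021 publications and the COVID-19 pandemic. It therefore cannot show that recruiters had read the block size, and a new list may come too late. Pain is also measured at baseline and analysed over repeated assessments, so selecting patients on ability to attend or use CDs need not shift the change in pain.

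Most of this stands, and it limits the claim. A reader might infer that a fifth of allocations actually were known in advance, or that concealment failed because a study author runs both education arms. The documents support neither inference. They do show that a single size was prescribed, that the arms are evident once assigned, and that nothing separates those who enrol from the block size or past assignments. The stated safeguards do not close that gap.

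**Conclusion.** The point holds as an avoidable weakness in the stated allocation method. In the two sequential settings worked through, the share of allocations certain in advance runs from about 0.25% (one sequence across centres, local view only) to 20% (block size and every earlier allocation in the block known). The best-guess rate runs from about 39% to 56%. If whole batches are enrolled before allocation, selection is not affected at all.

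The 20% is an upper limit. It rests on a 1:1:1 ratio within each block, sequential allocation, and a recruiter with full knowledge. The count is 18 or about 22 patients, depending on which of the protocol's two totals applies. No bias in the primary comparison has been shown, and its size cannot be estimated from the protocol.

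**What to change.** In Randomization description, replace the fixed size with permuted blocks of randomly varying size (for example 6 and 9), generated and held only by the outside research assistant. State that the sizes and the running allocation record are kept from those who enrol, and that each envelope is opened only after consent, eligibility and baseline measures are complete. The withholding step is essential, because varying the size alone leaves the best guess at about 54%. It would also help to say who enrols, whether blocks run within centre, and whether allocation is sequential or batched.

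The cost is a differently generated list and a possible imbalance of a few patients if recruitment stops inside a block: at most 3 between any two arms in a block of 9, since such a block holds three cards per arm.

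If recruitment is already complete, the list cannot be changed. The report should then state who enrolled patients, what they knew of earlier allocations, and whether allocation was sequential or batched.
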